## SUMMARY

**Rationale:** Lymph node metastasis of pelvic tumours are primarily found along the iliac vessels, the caval vein, aorta, obturator regions, and in the mesorectal and pre-sacral space. Surgical removal of these lymph nodes may be indicated, especially if abnormal on pre-operative imaging. Exact localization of lymph nodes during surgery, however, can be challenging, especially after previous treatment (chemo-radiotherapy and/or previous surgery). We have developed a surgical navigation system which can aid in the localization and removal of lymph nodes. Within the system, the pre-operative imaging information is linked to the actual anatomy during surgery. The navigation system has been evaluated in a pilot study. In 25 patients, 67 of the 71 targeted lymph nodes on pre-operative imaging were actually localized during surgery and removed. These promising results have led to the design of a prospective randomized controlled trial in which the beneficial value of the navigation system for abdominal lymph node dissections will be evaluated.

**Objective:** To assess the beneficial value of our electromagnetic navigation system for targeted lymph node dissection in the abdomen.

**Study design:** Randomized controlled clinical trial.

**Study population:** All patients aged 18 or older, scheduled for open abdominal surgery in which targeted removal of one or more pathological lymph nodes is part of the surgical plan.

**Intervention (if applicable):** After providing informed consent, patients will be randomized between conventional surgery and navigation assisted surgery. In the control arm patients will be operated according to current clinical practice. In the experimental arm, patients will be operated with assistance of a navigation system.

**Main study parameters/endpoints:** Primary endpoint will be the number of failed procedures, in which failure is defined as: presence of any residual target lymph node on follow-up imaging. Secondary endpoints are: time from having the surgical field prepared for lymph node localization to actual removal of the lymph node, overall surgical time, individual LN retrieval rate, blood loss, operator satisfaction, complications, cost, hospital stay, and health related quality of life.

We estimate 40% failed procedures in the conventional arm, vs. 16% in the navigation arm. To achieve sufficient scientific power, we will need 41 patients in each arm.

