### **Secondary Objective(s):**

As secondary endpoints we will evaluate:

- Time from having the surgical field prepared for lymph node localization to actual removal of the lymph node
- Individual LN retrieval rate
- Overall surgery time
- Blood loss
- Operator satisfaction using standard questionnaires
- Grade  $\geq 3$  morbidity
- Cost
- Hospital stay
- Health related quality of life, using QLQ-C30 (all patients), CR29 (colorectal patients), PR25 (urology patients), and EQ-5D-5L for cost effectiveness

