### 4.2 Inclusion criteria

In order to be eligible to participate in this study, a subject must meet all of the following criteria:

- Age  $\geq 18$
- Scheduled for open abdominal surgery
- Planned removal of at least 1 extra-regional lymph node suspect on imaging, as assessed by the specialist who will perform the operation
- Informed consent

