### 4.4 Sample size calculation

In the current pilot study (N13NAV), a total of 71 targeted lymph nodes were identified in 25 patients. In total, we failed to localize 4 of the 71 lymph nodes, in four separate patients. We therefore expect to have approximately 16% (4/25) failed procedures in the navigation arm ( $p_B=0.16$ ). In the current pilot study, surgeons indicated in at least 6 patients that certain localized lymph nodes would have not been found without navigation. We therefore estimate a failure rate of 40% ( $p_A=0.40$ ) in the control arm ((6+4)/25). In our study setup we test the following hypotheses  $H_0: p_A = p_B$  and the alternative hypothesis  $H_1: p_A > p_B$  (one-sided alpha). The number of

needed patients per arm with an alpha of 0.05 and a power of 80% is 41. Accrual of all patients is estimated to take 36 months (excluding the time to the first follow-up scan for all).

[figure not shown]

Fig. 2: Screenshot of the 3D anatomical model of a patient during navigation surgery in which the arteries (red), veins (blue), ureters (yellow), bones (white), and pathologic lymph nodes (lime) are shown. The tracked pointer is manipulated by the surgeon in the pelvis of the patient, and is shown in real-time within the 3D model (green). In this example a lymph node was localized in between the internal iliac artery, the internal iliac vein and the ureter

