#### **8.1.2 Secondary study parameters/endpoints**

Time to localization: to assess the time to localization, the surgeon will be asked to indicate when he/she is ready to start localizing a targeted LN. The start point is after opening the abdomen, clearance of adhesions, installation of an abdominal wall retraction device. Time will be recorded until the LN is localized, and also until the LN is removed.

Other parameters which will be recorded are: success rate of retrieved individual LNs, overall surgery time from start of surgery until the abdomen is closed again; blood loss; technical failures of the navigation system; and operator satisfaction using standard questionnaires. For health technology assessment, EQ-5D-5L, QLQ-C30, and QLQ-CR29 or QLQ-PR25 will be used before surgery, and at 3 and 12 months

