### 10.2 Secondary study parameter(s)

- Time from having the surgical field prepared for lymph node localization to actual removal of the lymph node: two-sample t-test,
- Overall surgery time: two-sample t-test
- The number of individual retrieved LN s in both arm, two-sample t-test
- Blood loss: two-sample t-test on all subjects
- Operator satisfaction: will be evaluated using standard questionnaires in the patients which are operated with navigation only. The questionnaire results in a score between 0 and 100. Technology which has a score 70 or higher is deemed beneficial [15].
- The QLQ and EQ-5D questionnaires are presented as a score from 0-100. Per arm these numbers will be handled as a continuous variable. We will also compare the change in the scores between T0 and T3 months, T0 and T6, and between T0 and T12 months at a patient level per arm. A two-sample t-test will be used for statistical evaluation

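### The individual lymph-node retrieval endpoint is named as a rate, but section 10.2 tests the number of nodes retrieved, which mainly reflects how many targets patients had and has low power

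*Protocol*

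**What the plan says.** The endpoint appears as a rate in three places of the protocol:

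- Summary: "individual LN retrieval rate"
- Section 2, secondary objectives: "Individual LN retrieval rate"
- Section 8.1.2: "success rate of retrieved individual LNs"

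Section 10.2 then fixes the analysis as "The number of individual retrieved LN s in both arm, two-sample t-test". It gives no denominator, and it does not say whether the test is one- or two-sided.

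The number of targets per patient is open upwards. Section 4.2 asks only for "Planned removal of at least 1 extra-regional lymph node suspect on imaging". In the pilot, section 4.4 reports that "a total of 71 targeted lymph nodes were identified in 25 patients". The number of targets is not a stratification factor in section 8.2. It is also not among the characteristics recorded in 8.1.3 and checked for balance in 10.3, although node size is.

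**The concern.** A rate and a count are different quantities. The count in a patient is the number of targets multiplied by the share retrieved, so an arm whose patients happen to have more targets scores higher whatever the quality of retrieval. For example, 2 targets per patient with 95% retrieved gives a mean of 2 × 0.95 = 1.9 nodes, while 3 targets with 80% retrieved gives 3 × 0.80 = 2.4. The worse retrieval rate has the higher count.

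Randomisation balances the number of targets on average, but with 41 patients per arm chance differences remain, and the planned test has no denominator to absorb them. Followed as written, the plan reports a difference in numbers of nodes where the objectives promise a comparison of retrieval rates, and it has much less chance of detecting a real improvement.

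**Working it through.** **The plan's own figure.** Section 4.4 plans on 40% against 16% failed procedures, one-sided alpha 0.05 and 80% power. With unpooled variance, n = (1.645 + 0.842)² × (0.40×0.60 + 0.16×0.84) / 0.24² = 6.18 × 0.3744 / 0.0576 = 40.2, so 41 per arm. The stated 41 reproduces. It belongs to the primary endpoint; the protocol gives no power for this secondary one.

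**Inputs from the protocol.** Mean targets per patient 71/25 = 2.84; 41 patients per arm; failed procedures 40% and 16%. The pilot retrieved 67/71 = 94.4% of nodes with navigation ("we failed to localize 4 of the 71 lymph nodes, in four separate patients").

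**Assumptions not in the protocol.**
- Distribution of targets N, each with mean 2.84. Low spread: 2, 3 or 4 nodes with probabilities 0.36, 0.44, 0.20, variance 0.36×0.84² + 0.44×0.16² + 0.20×1.16² = 0.53. Middle: 1 + Poisson(1.84), variance 1.84. High: 1 + geometric with mean 1.84, variance 1.84 + 1.84² = 5.23.
- Nodes succeed or fail independently within a patient.
- A node not retrieved is a residual node on follow-up imaging, so a procedure succeeds when all N nodes are retrieved.
- Two-sided 5% unless stated.

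**Calibration.** Choose the node retrieval rate p so that the mean of p^N is 0.60 (control) or 0.84 (navigation). In the middle case the mean of p^N is p × exp(−1.84(1−p)): p = 0.826 gives 0.60 and p = 0.939 gives 0.84. The navigation value agrees with the pilot's 94.4%.

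**Count test by formula, middle case.** For count X, Var(X) = p²Var(N) + p(1−p)E(N).
- Control: 0.826²×1.84 + 0.826×0.174×2.84 = 1.255 + 0.408 = 1.66.
- Navigation: 0.939²×1.84 + 0.939×0.061×2.84 = 1.622 + 0.163 = 1.79.
- The spread of targets therefore makes up 1.255/1.66 = 76% of the variance in control and 1.622/1.79 = 91% in navigation.
- Expected difference: 2.84 × (0.939 − 0.826) = 0.32 nodes. Standard error: √((1.66 + 1.79)/41) = 0.29. Ratio 1.11.
- Power two-sided: Φ(1.11 − 1.96) = 20%. One-sided: Φ(1.11 − 1.645) = 30%.
- Chance alone gives the difference in mean targets an SD of √(2×1.84/41) = 0.30, about as large as the effect.

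**Simulation of all three spreads** (at least 20,000 trials each):

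| | Low | Middle | High |
|---|---|---|---|
| Node retrieval, control / navigation | 0.833 / 0.940 | 0.826 / 0.939 | 0.810 / 0.937 |
| Share of count variance due to targets, control / navigation | 0.483 / 0.747 | 0.756 / 0.908 | 0.888 / 0.965 |
| Power, count t-test, two-sided | 37% | 20% | 12% |
| Power, count t-test, one-sided | 50% | 30% | 20% |
| Power, per-patient proportion, two-sided | 71% | 68% | 66% |
| Power, retrieved/targeted, patient-level variance, two-sided | 74% | 78% | 84% |
| Navigation has the lower mean count | 4% | 13% | 20% |

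A significant result in the wrong direction for the count occurs in at most 0.3% of trials. The pooled rate points the wrong way in about 0.3%. With no treatment effect, the count test rejects in 4.7% to 5.0%.

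**Sensitivity.** With a smaller assumed effect (61/71 against 67/71 nodes), power is 26% / 13% / 8% for the count, 56% / 49% / 42% for the proportion and 58% to 59% for the clustered ratio. With a within-patient correlation of 0.2 in the middle case, it is 25% for the count against 70% for the clustered ratio.

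**The case against.** The strongest reply is that 10.2 uses loose shorthand for the same endpoint. None of the three places that name a rate states a denominator, so reading it as retrieved over targeted is an inference, though a natural one: the pilot is reported as 67 of 71. Even so, the line fixes a variable and a test, and a statistician following it would analyse counts. That is an inconsistency in the protocol itself, not a detail left to a later analysis plan.

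Several stronger readings are tempting, and the documents do not support them.

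- *The count measures targets instead of retrieval.* The expected difference is 0.24 to 0.37 nodes per patient over the scenarios tried, so the count does carry treatment effect.
- *The test is biased or produces false positives.* Type I error stays near 5%, and a significant reversal is rare.
- *The test has almost no power.* The protocol gives neither the spread of targets nor the sidedness of this test. If the one-sided 5% level of the primary analysis applied here, power could reach about 50% with a low spread.
- *The plan ignores that nodes cluster within patients.* This would hold only for a node-by-node analysis, which 10.2 does not propose. A t-test on a number of nodes most naturally uses one count per patient.

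Two further limits stand. The 40% against 16% effect belongs to the primary endpoint. And non-retrieval at surgery need not coincide with a residual node on imaging: three of the four pilot misses were nodes that had shrunk below 3 mm.

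**Conclusion.** The mismatch is real: the endpoint is a rate, and the planned variable is a count without a denominator. The count test is valid under the null hypothesis, but it does not estimate the retrieval rate, and it loses much of the available power. The size of the loss depends on the assumed target distributions, independent nodes, the equation of non-retrieval with a residual node, and effects borrowed from the primary endpoint. The ordering (count well below proportion and clustered ratio) was the same in every scenario tried, so the direction is firm and the exact percentages are not.

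This concerns one secondary endpoint. The primary analysis, the sample size and the data collection are unaffected. It should be corrected, but it does not threaten the trial's main conclusion.

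**What to change.** Replace the line in 10.2 with: retrieved over targeted nodes, the denominator being the pre-operative target list, compared between arms with the patient as cluster (for example GEE with robust standard errors, or a ratio estimator with cluster-robust variance). At minimum, apply the t-test already planned to the per-patient proportion retrieved, which recovers most of the power. The two weight patients differently: the proportion gives each patient equal weight, the pooled ratio each node. The text should say which is meant.

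Keep nodes judged inoperable during surgery in the denominator, consistent with the intention-to-treat rule in 10.1. Report the number of targets per arm, and state whether the test is one- or two-sided.

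The cost is one changed line and slightly more analysis work. No new data are needed: section 8.3 already has the targets marked before surgery in all patients, 8.1.2 records retrieval of individual nodes, and 8.1.1 has each target checked on the follow-up scan.

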During the last few years we have developed an innovative electromagnetic navigation system that may comply with the challenges for intra-abdominal navigation. In our setup, reference sensors are placed on the patient surface just before surgery. Subsequently, an intra-operative CT is acquired with the patient in the surgical position. The intra-operative CT is used to link the 3D anatomical model, based on preoperative data, with the actual OR setup, and to the reference sensor positions. During surgery, a tracked pointer is used, which is visible in the abdomen, and also virtually in the 3D anatomical model. Organs at risk that are relatively rigid with respect to the reference sensors, such as the iliac vessels and a large part of the ureters, can be located accurately using the pointer. This is also valid for pathologic lymph nodes which are located near the large vessels, as well as for tumours which are rigid due to invasion of pelvic structures. This system is being evaluated in an ongoing feasibility study (N13NAV, NL43553.031.13) for a wide range of indications. In this study, so far 37 patients have been included. We started with inclusion of only colorectal patients (n=21), but enthusiastic feedback and interest from other disciplines resulted in widening of the inclusion to patients with urologic (n=12), gynaecologic (n=1) and sarcoma tumours (n=3). In these procedures the navigation system was used to localize the borders of 4 primary tumours (all radical resections) and 6 local recurrences (5 radical resections). Furthermore, in 25 patients a total of 71 extra-regional LNs were identified on preoperative imaging. Of the 71 LNs, 67 were successfully retrieved using the developed navigation technique. Of the remaining 4 LNs, three in the obturator region were diminished to a size of less than 3 mm after neoadjuvant chemo-radiation. The fourth LN, originating from the prostate, was located within the mesorectum and was probably displaced during surgery. The different surgical disciplines adopted the navigation system rapidly, and provide patients to include in the study on a regular basis.

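### Section 10.2 fixes unadjusted two-sample t-tests for node-removal time, surgery time and blood loss, although randomisation is stratified by surgical sub-specialty

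*Protocol*

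**What the plan says.** Section 10.2 names one test for each of three continuous secondary outcomes:

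- time from prepared surgical field to node removal: "actual removal of the lymph node: two-sample t-test"
- "Overall surgery time: two-sample t-test"
- "Blood loss: two-sample t-test on all subjects"

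It mentions no covariate, stratum, transformation or fallback, and does not state whether these tests are one- or two-sided.

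Section 8.2 stratifies randomisation by three sub-specialties (surgery, urology, gynaecology). The reason given is that they may approach the target nodes differently.

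Section 8.1.2 says how the outcomes are recorded: "overall surgery time from start of surgery until the abdomen is closed again; blood loss". Nowhere does the protocol give a mean, SD, skewness, expected difference or power for them. The sample size rests on the binary primary endpoint alone; the Summary states "we will need 41 patients in each arm".

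**The concern.** Stratified randomisation balances the strata between arms, so differences between sub-specialties largely cancel out of the treatment comparison. An unadjusted t-test does not know this. It leaves the between-stratum variation in its residual variance, so the standard error and confidence interval are wider than the design warrants. The true error rate falls below nominal and power is lost.

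Overall surgery time runs from the start of surgery to closure, so it includes whatever else the operation involves. That could plausibly differ between a surgical, a urological and a gynaecological case. Section 5.1 hypothesises faster localisation, and the number of patients was not chosen with these outcomes in mind. The analysis model is therefore the available means of protecting their precision.

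**Working it through.** **1. The plan's own figure.** Section 4.4 states "needed patients per arm with an alpha of 0.05 and a power of 80% is 41", with failure rates of 0.40 and 0.16 and a "one-sided alpha". The unpooled formula gives

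n = (1.645 + 0.842)² × (0.40×0.60 + 0.16×0.84) / 0.24² = 6.18 × 0.3744 / 0.0576 = 40.2, so 41 per arm.

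The pooled-variance formula gives 43. The stated 41 is reproduced, and it contains nothing about times or blood loss.

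**2. Effect of leaving the stratum out.** Inputs: 41 per arm (protocol); two-sided 5% for the secondary tests (assumed); stratum shares 23/14/4 per arm, equal in both arms (assumed); within-stratum SD = 1; stratum means differing by d SD (assumed).

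With stratum proportions w and means m:

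- between-stratum variance B = Σwm² − (Σwm)²
- true standard error of the difference = √(2/41) = 0.221
- standard error used by the unadjusted test = 0.221 × f, where f = √(1 + B)
- type I error ≈ 2Φ(−1.96 f)
- power ≈ Φ(2.80 − 1.96 f), at an effect giving the adjusted analysis 80% (2.80 = 1.96 + 0.84; effect 2.80 × 0.221 = 0.62 SD)

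Evenly spaced means (0, d, 2d): Σwm = 22d/41 = 0.537d, Σwm² = 30d²/41 = 0.732d², so B = 0.444d². Two levels (0, d, d): B = (18/41)(23/41)d² = 0.246d².

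As a check on the shares, the pilot had 21 colorectal, 12 urologic, 1 gynaecologic and 3 sarcoma patients (section 1). Counting sarcoma as surgery and scaling to 41 gives 24/37, 12/37 and 1/37, about 27/13/1. With evenly spaced means, B = 17d²/41 − (15d/41)² = 0.281d².

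| Shares, spacing | d | f | Type I error | Power (adjusted 80%) |
|---|---|---|---|---|
| 23/14/4, even | 0.5 | 1.054 | 3.9% | 77% |
| 23/14/4, even | 1.0 | 1.202 | 1.9% | 67% |
| 23/14/4, two levels | 0.5 | 1.030 | 4.3% | 78% |
| 23/14/4, two levels | 1.0 | 1.116 | 2.9% | 73% |
| 27/13/1, even | 0.5 | 1.035 | 4.3% | 78% |
| 27/13/1, even | 1.0 | 1.132 | 2.7% | 72% |

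A simulation with shares 23/14/4 agrees. The unadjusted t-test had type I error of 4.2% and 1.8%, and power of 78% and 71%, at shifts of 0.5 and 1 SD. The stratum-adjusted model held about 5% and 81%. The loss is therefore 2 to 3 points at 0.5 SD and about 10 points at 1 SD (7 to 13 across the layouts above).

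**3. Whether a log scale adds to this.** Simulated power at 41 per arm, two-sided 5%, no strata:

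| Assumed data | Ratio | t-test, raw values | t-test, log values |
|---|---|---|---|
| Log-normal, log-SD 0.5 | 0.7 | 85% | 89% |
| Log-normal, log-SD 0.8 | 0.7 | 40% | 51% |
| Log-normal, log-SD 1.0 | 0.7 | 25% | 36% |
| Gamma, shape 1 (skewness 2) | 0.6 | 61% | 44% |
| Gamma, shape 2 (skewness 1.4) | 0.6 | 89% | 81% |

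When the ratio is set so that the log analysis has about 80% power, the log-normal gain is only 1 to 5 points at log-SD 0.2 to 0.5. For gamma-shaped data the ordering reverses. In the null log-normal cases the raw t-test's type I error was 4.0% to 5.1%, so skew did not inflate it.

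**The case against.** The strongest reply is that section 10.2 contains no error. The t-test keeps its error rate at or below nominal, the outcomes are unpowered secondaries, and a separate analysis plan may refine the model. The first two parts stand: this is about precision, not validity. The third stands only in part, because the protocol names a specific test for each outcome rather than leaving the choice open, so a stratum-adjusted model would depart from what it states.

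A second reply is that the sub-specialties may not differ on these outcomes. That is possible, since the documents give no data. The adjusted model then costs two degrees of freedom out of 80, which is negligible.

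A reader might infer something stronger: that times and blood loss are bound to be right-skewed, so the t-test is the wrong test and logs would recover the lost power. The documents do not support this. They give no distribution, and section 10.2 names no scale. The direction of the gain depends on the shape of the skew, as the gamma results show, and for mildly skewed surgery time the choice hardly matters. Logs also change the question to a ratio of geometric means. With equal arithmetic means but unequal spread (log-SD 0.8 against 0.5), the log test rejected 26% of the time and the raw test 6%. That matters because cost is also a secondary endpoint, and total resource use follows arithmetic means.

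A reader might also infer that the trial sets out to show less blood loss. No section hypothesises that; blood loss is only listed as an outcome. The stated hypothesis in section 5.1 is more successful and faster localisation.

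**Conclusion.** The point holds as a modest, nearly free improvement to secondary analyses. The protocol stratifies by sub-specialty for a stated reason and then fixes tests that ignore the stratum. If these outcomes differ between sub-specialties, standard errors are too large, by roughly 3% to 5% at a 0.5 SD shift and 12% to 20% at 1 SD. Power falls by about 2 to 3 and about 10 points respectively, and type I error drops below 5%.

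These sizes rest on assumed stratum shares, assumed shifts, balanced strata and two-sided 5% testing; none of these figures is in the protocol. With no stratum differences there is no loss. The case for changing scale is conditional and does not justify replacing the main analysis. The primary comparison and the 41 per arm are not affected.

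**What to change.** In section 10.2, replace the three t-tests with a linear model for each outcome containing treatment arm and randomisation stratum (surgery, urology, gynaecology). Report the adjusted difference between arms with its confidence interval, and state whether the test is two-sided. The effect stays in minutes or millilitres.

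Optionally, for blood loss and time to node removal only, add a log-scale sensitivity analysis with the same stratum term, reported as a ratio of geometric means with its confidence interval. The rule for zero values should be written down before the data are seen. Describe this as a check on robustness to skew, not as the more powerful analysis. The scale change does not settle how nodes that are never removed enter time to removal; that needs its own rule on either scale.

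The cost is one or two sentences, two degrees of freedom, and no additional patients or data, since the stratum is already entered at randomisation.

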**Nature and extent of the burden and risks associated with participation, benefit and group relatedness:** Patients will be asked to take quality of life and side effects questionnaires before surgery and at 3, 6 and 12 months after surgery. All patients will undergo one extra baseline contrast enhanced CT scan in the two weeks before surgery. For patients in the experimental arm, the CT scan is used to generate a 3D model of the anatomy. In the experimental arm, one intra-operative CT will be acquired to calibrate the navigation system. In both arms, the pre-operative CT might result in one

additional visit to our hospital. The surgeon is responsible for interpretation of the navigation system, and translation to surgical actions, therefore no additional risks are associated with participation.

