## **3. STUDY DESIGN**

This study is designed as a prospective randomized controlled trial (Fig. 1). After giving informed consent, patients will be randomized between conventional surgery without navigation (control arm), and the experimental arm with navigation. Patients will be asked to answer health-related quality of life questionnaires before surgery, and at 3, 6 and 12 months after surgery. Included

patients are part of this study from the first trial related procedure, until 30 days after surgery, even though the questionnaires will take place up to 12 months after surgery. This is because navigation related complications will not take place after the first 30 days. All patients will undergo an additional baseline CT scan with intra-venous contrast in the 2 weeks before surgery. This scan will be used to assess the target LNs. In the experimental arm the CT scan will be used to create a 3D model of the pelvic anatomy including the target LNs.

[figure not shown]

Fig. 1: outline of the study

We have chosen for a randomization setup to have minimum selection bias in the comparison between navigation and conventional surgery. Having a control arm is certainly valid, since the navigation setup is still experimental.

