## 5. TREATMENT OF SUBJECTS

All included patients are already scheduled for surgery. Participation will not influence the waiting time. If patients decide to participate, additional burden is dependent on randomization. All patients will be asked to take quality of life and side effects questionnaires before surgery and at 3 and 12 months after surgery. The questionnaires take approximately 20 minutes per time point.

Patients who are randomized to the conventional arm will be operated according to current clinical practice. These patients will undergo one additional CT scan with contrast (10 minutes) in the two weeks before surgery on which the target lymph nodes will be indicated. In the control arm, no 3D anatomical models will be generated.

Patients in the experimental arm will be operated with assistance of the in-house developed navigation system. One extra contrast enhanced CT scan before surgery will be acquired in the two weeks before surgery (10 minutes). During surgery, three Patient Trackers are attached to the skin of the patient using medical tape, not obstructing the surgical field. An additional intra-operative CT scan is acquired ( $\pm 10$  minutes) for calibration, which will be an addition to the total time of

anaesthesia. The surgeon will have a sterile tracked navigation pointer which can be used to correlate the actual anatomy of the patient with a 3D model derived from pre-operative imaging (Fig. 2). With this setup, the surgeon is provided with a view beyond surgical plane. After opening the abdomen, some anatomical landmarks will be used to verify the navigation accuracy, which will take a maximum of 5 minutes. Subsequently, the navigation system can be used to localize the targeted lymph nodes.

We will try to plan the additional pre-operative CT scan on a day at which the patient is already scheduled to visit our hospital to limit the travel time. Logistical challenges might result in an additional hospital visit.

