### **12.5 Temporary halt and (prematurely) end of study report**

The investigator/sponsor will notify the accredited METC of the end of the study within a period of 8 weeks. The end of the study is defined as the last patient's last visit (follow-up scan).

The sponsor will notify the METC immediately of a temporary halt of the study, including the reason of such an action.

In case the study is ended prematurely, the sponsor will notify the accredited METC within 15 days, including the reasons for the premature termination.

Within one year after the end of the study, the investigator/sponsor will submit a final study report with the results of the study, including any publications/abstracts of the study, to the accredited METC.

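### Two of the four stated questionnaire schedules omit month 6, so the planned T0–T6 quality-of-life comparison may have no data; the fixed t-tests are valid but less efficient than adjusting for baseline

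*Protocol*

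**What the plan says.** The questionnaire schedule is stated four times in the protocol:

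- Summary: "questionnaires before surgery and at 3, 6 and 12 months after surgery".
- Section 3: "questionnaires before surgery, and at 3, 6 and 12 months after surgery".
- Section 5: "questionnaires before surgery and at 3 and 12 months after surgery".
- Section 8.1.2, which defines the endpoint: the instruments "will be used before surgery, and at 3 and 12 months".

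Section 10.2 treats the scores as continuous and then adds change scores: "We will also compare the change in the scores between" T0 and 3 months, T0 and 6 months, and T0 and 12 months. The test is fixed: "A two-sample t-test will be used for statistical evaluation". No adjustment for the baseline score is mentioned. Section 2 lists the EQ-5D-5L for cost-effectiveness. Section 8.2 stratifies randomisation by surgical subspecialty.

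On timing, section 3 keeps patients in the study "until 30 days after surgery, even though the questionnaires will take place up to 12 months after surgery". Section 12.5 ends the study at the last patient's "last visit (follow-up scan"), and section 8.3 places that scan within 3 months of surgery.

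**The concern.** Section 10.2 analyses a time point that two of the four schedule statements do not collect. Those two are the sections staff are most likely to work from: what patients undergo (section 5) and how the endpoint is defined (8.1.2). A quality-of-life score at 6 months cannot be obtained afterwards, and an analysis plan cannot repair this, because it is an instruction on data collection. At stake are one of the three planned change comparisons and the middle point of the EQ-5D profile, which would otherwise have a nine-month gap between months 3 and 12.

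The second matter is the choice of test. The baseline score is collected from every patient, yet the protocol commits to unadjusted two-sample t-tests. With 41 patients per arm, and fewer for the colorectal and prostate modules because each goes to one patient group only, precision is worth having where it costs nothing.

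**Working it through.** **Schedule.** The statements side by side:

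| Place | 3 months | 6 months | 12 months |
|---|---|---|---|
| Summary | yes | yes | yes |
| Section 3 | yes | yes | yes |
| Section 5 | yes | no | yes |
| Section 8.1.2 | yes | no | yes |
| Section 10.2 (analysis) | yes | yes | yes |

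Two of the four collection schedules supply nothing for the T0–T6 contrast. The T0–T3 and T0–T12 contrasts are covered by all four.

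**Sample size available.** The protocol gives no sample size, SD, effect size or baseline correlation for quality of life. The 41 per arm comes from the primary endpoint (section 4.4: failure rates 0.40 and 0.16, one-sided alpha 0.05, power 80%). It reproduces with unpooled variances: (1.645 + 0.842)² × (0.40×0.60 + 0.16×0.84) / 0.24² = 40.2, rounded up to 41. Nothing here alters it.

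**Efficiency of the tests.** Assumptions that are not in the protocol: equal SD at baseline and follow-up, and baseline–follow-up correlation r. In units of the score variance, the relevant variances are:

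- change score: 2(1 − r)
- follow-up score alone: 1
- ANCOVA: 1 − r²

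ANCOVA relative to the change score is therefore (1 − r²) / [2(1 − r)] = (1 + r)/2. Because section 10.2 introduces the change scores as an addition to the scores themselves, I take both raw and change scores to be tested. The fair comparator is then whichever of the two has the smaller variance.

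| r | Change | Follow-up alone | ANCOVA | ANCOVA / change | Better planned test / ANCOVA |
|---|---|---|---|---|---|
| 0.3 | 1.40 | 1 | 0.91 | 0.65 | 1.00/0.91 = 1.10 |
| 0.5 | 1.00 | 1 | 0.75 | 0.75 | 1.00/0.75 = 1.33 |
| 0.7 | 0.60 | 1 | 0.51 | 0.85 | 0.60/0.51 = 1.18 |
| 0.9 | 0.20 | 1 | 0.19 | 0.95 | 0.20/0.19 = 1.05 |

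The last column says that ANCOVA is worth about 10%, 33%, 18% and 5% more patients. The change score is worse than ignoring baseline altogether only when r is below 0.5.

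The detectable difference in SD units with 41 per arm, at two-sided 5% and 80% power (sidedness is assumed, since section 10.2 states none for these tests), is (1.960 + 0.842) × √(2v/41), where v is the variance above:

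- follow-up alone: 0.62 at every r
- change score: 0.73, 0.62, 0.48 and 0.28 at r = 0.3, 0.5, 0.7 and 0.9
- ANCOVA: 0.59, 0.54, 0.44 and 0.27

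**End of study.** If the last patient's scan is at 3 months, that patient's 12-month questionnaire is due 12 − 3 = 9 months after the formal end; with a scan at 1 month, 12 − 1 = 11 months. Assuming even accrual over the 36 months in section 4.4, the patients with a 12-month questionnaire due after the formal end number 9/36 = 25% (about 20 of 82) or 11/36 = 31% (about 25 of 82). Section 12.5 allows one year from the end of study for the final report, so the last questionnaire still arrives 12 − 9 = 3 months, or 12 − 11 = 1 month, before that deadline.

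**The case against.** The strongest reply concerns everything except the schedule. Quality of life is secondary and unpowered. The t-tests are valid under randomisation, and a fully specified model is commonly left to an analysis plan that is not shown here. This stands in part. The t-test is not an error, and baseline adjustment is a recommendation. But the protocol does not leave the test open: it names one, so the choice can be questioned here.

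Three stronger readings are tempting, and the protocol does not support them:

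- *That the t-tests waste the baseline.* They do not. A change score uses the baseline with its coefficient fixed at 1; the loss is one of efficiency. Nor do separate tests at each visit discard a patient who misses one questionnaire: that patient still counts at the other visits.
- *That adjustment brings the precision of 18% to 54% more patients.* Those figures are 1/0.85 and 1/0.65, for r = 0.7 and 0.3. They compare ANCOVA with the change score alone. At r = 0.3 the planned raw-score test already does better, and the gain over it is about 10%. They also omit high correlations, where little is gained.
- *That the study ends before the 12-month data and so loses them.* Section 3 openly says that questionnaires continue to month 12 and explains the 30-day limit by the absence of later navigation-related complications. Section 12.5 sets the date for notifying the ethics committee; it does not stop collection.

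On the schedule itself I see no defence. All the statements are current text, and they disagree.

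**Conclusion.** The schedule contradiction is certain and rests on no assumption. The Summary and sections 3 and 10.2 include month 6; sections 5 and 8.1.2 do not. The protocol does not show which schedule is in use, so the loss is conditional: if sections 5 and 8.1.2 are followed, the T0–T6 comparison and the 6-month EQ-5D point do not exist for any of the 82 patients. It should be corrected before questionnaires fall due.

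The test choice is valid and can be improved at no cost in data. The size of the gain depends on a correlation the protocol does not give and on equal SDs: about 5% to 33% more patients against the better planned test for the values of r shown. The primary endpoint and its sample size are untouched.

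The end-of-study wording is a minor mismatch to tidy, and no data loss follows from it.

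**What to change.** 1. State one questionnaire schedule in the Summary and sections 3, 5, 8.1.2 and 10.2. Keep the T0–T6 contrast only if that schedule contains month 6. The cost is protocol wording; there is no new data collection if the 3, 6 and 12-month schedule is already in use.
2. In section 10.2, replace the t-tests on quality-of-life scores by ANCOVA of the follow-up score on arm, baseline score and subspecialty (the stratification factor), visit by visit, or by a repeated-measures model with the same terms. For the colorectal and prostate modules the subspecialty term will carry little, since each module goes to one patient group. This needs no extra data.
3. Align the end-of-study definition in 12.5, and the 30-day statement in section 3, with the last scheduled questionnaire, or say explicitly that questionnaire collection continues beyond the formal end. Moving the definition makes the formal end date later; an explanatory sentence costs nothing.
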